## Abstract

**Introduction:**

Selective fetal growth restriction (sFGR) is a major cause of perinatal morbidity and mortality in monochorionic diamniotic (MCDA) twin pregnancies. Current management relies on umbilical artery Doppler patterns in the smaller twin. These patterns are, however, inconsistent and do not represent a reliable severity scale, complicating clinical decision-making and parental counselling. This study aims to improve risk stratification by identifying predictors of adverse outcomes, while also evaluating the pathophysiology and multi-organ impact of sFGR in early childhood.

**Methods and analysis:**

This is a prospective, international, multicentre cohort study conducted in six tertiary fetal medicine centres with expertise in complicated twin pregnancies. Recruitment began in March 2023 and will continue until December 2026, targeting 274 MCDA twin pairs with complete follow-up to develop a prediction model for adverse perinatal outcomes in sFGR at the time of diagnosis. Standardised data collection includes serial ultrasound examinations, advanced fetal imaging (cardiac, cerebral and 3D volumetric), fetal brain MRI and detailed placental phenotyping. Maternal and parental well-being are assessed during pregnancy and after birth. Neurodevelopmental outcome is evaluated up to 2 years after birth using validated tools. The statistical analysis plan includes predictive modelling with internal validation.

**Ethics and dissemination:**

The study has been approved by the ethical review boards of all participating centres. Findings will be disseminated through peer-reviewed publications, international conferences and engagement with clinical guideline committees.

**Trial registration number:**

NCT05952583.

STRENGTHS AND LIMITATIONS OF THIS STUDYProspective, international multicentre cohort design with standardised study data collection across six fetal medicine centres.Harmonised, quality-controlled imaging protocol across centres, with regular audits, including advanced ultrasound, 3D volumetry and fetal MRI.Standardised placental phenotyping and parental well-being assessments from prenatal to postnatal stages.Observational design, limiting causal inference.Recruitment in tertiary care centres may be biased towards severe cases; international differences in referral/management and loss to follow-up are anticipated.

## Introduction

 Selective fetal growth restriction (sFGR) complicates approximately 15%–20% of monochorionic diamniotic (MCDA) twin pregnancies and is defined by substantial discordant growth between the twins.^1^ It is associated with high risks of intrauterine death and severe neonatal morbidity in one or both twins.^1^ Management is particularly challenging, as clinicians must weigh the benefits of prolonging gestation against the risks of fetal deterioration, death and morbidity in the co-twin resulting from a very preterm delivery. Although fetal interventions such as selective reduction or cord occlusion may be considered in selected severe cases, no curative treatment exists. As no curative treatment exists, timely delivery to save both twins remains the only intervention, making accurate outcome prediction essential.

Current management is based on the classification of umbilical artery Doppler patterns in the smaller twin (type I to III).^2^ Although associated with distinct prognoses, these patterns can vary considerably during pregnancy and do not represent a progressive severity scale.^2^,^12^ This uncertainty complicates both delivery timing and parental counselling. Improved risk stratification is therefore needed. A severity-based prediction model that integrates ultrasound parameters could better distinguish between mild and severe clinical courses, supporting individualised management, more precise counselling and ultimately improved outcomes.

In addition to improving prediction of the clinical course, it is also important to recognise that the effects of sFGR extend beyond growth itself, with potential consequences for vital organ development and long-term outcomes. Limited evidence suggests cardiac adaptation in both twins, including hypertrophy in the larger twin and impaired ventricular function in the smaller twin, as well as an increased risk of congenital heart disease.^13^,^15^ Neurodevelopmental effects are even less well understood. In singletons with growth restriction, altered brain structure and connectivity have been demonstrated, but systematic evaluation in MCDA twin pregnancies is lacking.^16 17^ Emerging data suggest impaired neurodevelopment in growth-restricted twins,^18^ yet outcomes in single survivors remain largely unknown. The genetically identical co-twin design offers a unique opportunity to study these effects while controlling for genetic and gestational confounders.

Another important but incompletely understood aspect of sFGR is its pathophysiology. Unequal placental sharing plays a central role, leaving one twin with reduced nutrient and oxygen supply.^19^,^22^ Yet, sFGR develops only in a proportion of such pregnancies,^23^ suggesting that additional mechanisms are involved. These may include differences in placental vascular architecture: type III placentas often feature large artery-to-artery anastomoses and extensive shared intertwin circulation, whereas these are typically absent in type II.^2024^,^26^ Whether placental dysfunction—particularly affecting the smaller twin—contributes to the pathophysiology of sFGR remains unclear. However, systematic histopathological studies have not yet been conducted, and correlating these with antenatal imaging could provide valuable insights into disease mechanisms.

Finally, the psychological impact of sFGR on parents remains largely unexplored. Twin pregnancies are already associated with increased stress and depressive symptoms,^27 28^ yet little is known about how sFGR affects parental well-being and attachment patterns before and after birth.

To address these gaps, the CONTRAST study brings together leading fetal medicine centres in Europe and North America. Its primary aim is to develop a prediction model for adverse outcomes in sFGR at the time of diagnosis. Secondary aims are to evaluate the impact on fetal organ development and long-term neurodevelopment, investigate associations between antenatal findings, placental pathology and outcome, and examine parental psychological well-being and attachment. This prospective collaboration seeks to advance the understanding, classification and management of sFGR and ultimately improve outcomes for affected families.

## Methods and analysis

### Study design and setting

The CONTRAST study is an ongoing international, prospective, multicentre cohort study in MCDA twin pregnancies complicated by sFGR. Six tertiary fetal medicine centres participate: Leiden University Medical Center (Netherlands), University Hospitals Leuven (Belgium), Karolinska University Hospital (Sweden), BCNatal (Spain), Boston Children’s Hospital (USA) and Mount Sinai/Hospital for Sick Children (Canada).

### Eligibility

We include MCDA twin pregnancies with sFGR diagnosed before 28 weeks’ gestation, regardless of umbilical artery Doppler flow pattern. sFGR is defined as a persistent (observed during ≥two consecutive ultrasound examinations) estimated fetal weight (EFW) discordance of ≥20% between the twins, in the absence of twin-to-twin transfusion syndrome (TTTS) or twin anaemia–polycythaemia sequence (TAPS) at time of inclusion.

This sFGR definition enables consistent inclusion across centres regardless of growth chart usage and aligns with clinical practice, whereas the more complex Delphi consensus criteria^29^ have shown limited adoption and similar predictive accuracy.^30^ Recent data further support intertwin EFW discordance as a stronger predictor of adverse outcome than centile-based definitions in monochorionic twins.^31^ An EFW discordance threshold of ≥20% is associated with increased perinatal risk and robust predictive performance,^31^,^34^ allowing consistent application across centres. The upper inclusion limit of 28 weeks’ gestation was selected to capture both early and later presentations of sFGR, thereby enhancing the clinical relevance and generalisability of the prediction model.

EFW discordance is calculated as (EFW larger twin–EFW smaller twin)/EFW larger twin×100.TTTS is defined by the presence of discordant amniotic fluid volumes, with a maximum vertical pocket >6 cm before 16 weeks, >8 cm at 16–20 weeks or >10 cm after 20 weeks in one sac and <2 cm in the co-twin, accompanied by a distended bladder (defined as persistently visible and subjectively enlarged on ultrasound) in the recipient and an absent or small bladder in the donor twin.^35^,^37^TAPS is defined by a discordance in middle cerebral artery peak systolic velocity >0.5 multiples of the median, which may be accompanied by supportive features such as placental dichotomy or a ‘starry-sky’ appearance of the fetal liver in the anaemic twin.^38^

Both parents must be ≥18 years and able to provide informed consent. Pregnancies with fetuses affected by lethal anomalies or explicitly referred for a fetal intervention without follow-up are excluded.

### Study procedures

Participants are followed from diagnosis at the tertiary care centre until 24 months of age, corrected for premature birth, with data collected across three phases (figure 1). Throughout the study, collaboration within a multidisciplinary team—including fetal medicine specialists, perinatal pathologists, neonatologists and paediatric neuropsychologists—supports consistent data collection and strengthens both study design and interpretation.

**Figure 1 F1:**
[figure not shown]
An overview of the main assessments that participants in the sFGR cohort will undergo during the research. sFGR, selective fetal growth restriction.

### Phase I: prenatal

All participants receive routine clinical care for MCDA twins according to local protocols. In addition, standardised ultrasound measurements such as umbilical venous Doppler flow, cardiac function, assessment of placental structure and fetal brain development are collected at inclusion (T1), 20–22 weeks (T2) and 28–30 weeks’ gestation (T3) (table 1). If inclusion coincides with the second time point (20–22 weeks), only two assessments are performed. A full list of the ultrasound parameters is provided in table 2. Fetal MRI is scheduled at 28–30 weeks’ gestation, currently implemented at selected centres, with ongoing expansion planned across all sites. The acquisition details of the different antenatal images are detailed in table 2. Regular quality audits are performed to monitor imaging, data entry and adherence to study procedures, thereby ensuring consistency and data integrity. Parental psychological well-being is assessed using validated questionnaires at inclusion and at 30 weeks of gestation (figure 2).

**Table 1 T1:** Timing of ultrasound and fetal MRI assessments

GA (weeks)	Standard measurements*	Additional measurements				
		Flow	Placental assessment	Cardiac assessment	Cerebral assessment	Fetal MRI
Inclusion (<28) (T1)	Routine ultrasound (local protocol)	UV: flow and diameter	AA-anastomosis: flow and diameter Placental appearance	CT-ratio In/outflow times TV regurgitation 4C-clip		
20–22 (T2)	Routine ultrasounds (local protocol)	UV: flow and diameter	Placental appearance	CT-ratio In/outflow times TV regurgitation 4C-clip	Still images 3D volume (20–24 weeks)	
22–28	Routine ultrasounds (local protocol)					
28–30 (T3)	Routine ultrasounds (local protocol)	UV: flow and diameter	Placental appearance	CT-ratio In/outflow times TV regurgitation 4C-clip	Still images (28–32 weeks) 3D volume (28+0 weeks)	Fetal MRI (28–30 weeks)
30–delivery	Routine ultrasounds (local protocol)					

* Standard measurements are tailored to local protocol and patient needs.

4C, four-chamber view; CT, cardio-thoracic; 3D, three-dimensional; GA, gestational age; TV, tricuspid valve; UV, umbilical vein.

**Table 2 T2:** Summary of image acquisition

Parameter	Acquisition details*		
Umbilical vein (UV)	Diameter: transverse abdominal section with spine left/right, UV horizontal; measure inner–inner vessel wall edges.	[figure not shown]	[figure not shown]
	Flow: spine up/down; pulsed-wave Doppler in mid-abdominal portion; insonation angle ≤30° (ideally 0°).		
		UV diameter (left) and UV flow right).	
Artery-to-artery (AA)	Placenta aligned with insonation angle; use color Doppler to detect bidirectional flow pattern; placenta perpendicular for diameter measurement.		
	Placental appearance	Sweep placenta; assess contrasting appearance (thickness and heterogeneity) between shares.		[figure not shown]
Cardiothoracic ratio (CT ratio)	[figure not shown]	4C transverse view with whole thorax visible: horizontal septum, complete rib, no abdominal contents/skin. Measure at end-diastole (closed valves). CT ratio = heart circumference / thorax circumference.	
		Continuous ellipse: thoracic circumference Discontinuous ellipse: cardiac circumference	
Four chamber clip (4C clip)	4C apical/basal; clear myocardial walls; ≥60 frames/s; record ≥5–6 s clip with good angle and high frame rate. Clip of at least 5-6 seconds with good angle and high frame rate		
Inflow/ outflow times	Angle 0° if possible (no angle correction). Capture whole cardiac cycle (3–5 waves). Measure: velocity (E, A waves), inflow time, peak velocity (outflow), cycle time	[figure not shown]	[figure not shown]
	White line: Inflow/Outflow time (respectively left and right image). Yellow line: whole cycle time.		
Tricuspid valve regurgitation	Pulsed-wave Doppler across TV, angle <30° to septum; high sweep speed; measure peak velocity (cm/s).		
Cerebral stills: transverse plane	Transthalamic plane: head circumference. Transventricular plane: both ventricles. Transcerebellar plane: transcerebellar diameter + cisterna magna.		
	Transthalamic plane for measurement of head circumference . Transcerebellar plane for measurement of transcerebellar diameter and cisterna magna. Transventricular plane for measurement of distal lateral ventricular width.		
	Cerebral stills: midsagittal plane	Measure: CC length (in–in), fastigium–CC genu, pons width (AP), vermian height (sup–inf lobule).		
[figure not shown]		Midsagittal plane for measurement of corpus callosum length, corpus callosum to fastigium distance, vermian height and pons diameter.	
3D cerebral volume	Central axial at thalami; insonation angle ~70° to include skull. Acquire (~4 seconds) 3D volume per twin		
Fetal MRI core sequences	T2-weighted (axial/coronal/sagittal, 2–4 mm slice). T1-weighted (transverse). Diffusion-weighted (1–2 planes). Hemosiderin-sensitive (SWI or T2* EPI). 3D volumetric sequences.		

* Five centres use Voluson E22 machines (GE Healthcare) for ultrasound acquisition and one centre uses Canon APLIO i800/i700 machines (Canon Medical Systems). Fetal MRI scanner characteristics are recorded per examination. Standardised acquisition protocols and regular quality audits are used to ensure consistency across centres.

AP, anteroposterior; CC, corpus callosum; DWI, diffusion-weighted imaging; EPI, echo planar imaging; E wave, early ventricular filling wave; SSFSE, single-shot fast spin-echo; SWI, susceptibility-weighted imaging; T1, T1-weighted sequence; T2, T2-weighted sequence.

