#### Secondary outcomes

Perinatal morbidity and mortality.Cardiac adaptation in both twins.Fetal brain development and neurodevelopment at 24 months.Correlation between antenatal and postnatal brain imaging.Placental architecture (gross and histological).Impact on parental mental health and attachment.Impact of management protocol differences across centres on primary outcome.

The secondary study parameters are outlined in table 3.

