### Data analysis plan

The primary analysis will develop a multivariable logistic regression model predicting the composite outcome at diagnosis. Model performance will be evaluated by discrimination (C-statistic) and calibration (scaled Brier score), with internal validation by bootstrapping.

Secondary analyses will include:

Longitudinal modelling of ultrasound trajectories using mixed-effects models (continuous variables) and generalised estimating equations (GEE) (categorical variables), with stratification by gestational age at diagnosis (according to the most recent literature-based cut-offs) and umbilical artery Doppler flow type.Associations between antenatal imaging and placental pathology.Comparison of neurodevelopmental outcomes between co-twins using GEE or paired t-tests.Parental well-being was analysed across timepoints using mixed-effects models.Comparison of outcomes between outpatient- and inpatient-managed pregnancies.

All tests will be two-sided, with p<0.05 considered significant. Analyses will be conducted in SPSS V.25 (IBM, Chicago, USA) and/or R.

Missing data will be minimised through prospective monitoring, regular quality audits and data queries to participating centres. For the primary composite outcome, missing delivery or fetal outcome data will be actively retrieved where possible; pregnancies with unascertainable primary outcomes will be excluded from the primary prediction model analysis. For missing predictor variables, recovery from source imaging or clinical records will be attempted. If data remain missing, appropriate statistical methods will be applied based on the extent and pattern of missingness, in line with best practice for prediction modelling. Missing questionnaire data will be addressed through reminders; incomplete questionnaires will be excluded from the relevant secondary analyses, with the degree of missingness reported.

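### The text and Table 1 disagree on fetal brain imaging at inclusion; if sites follow the table, pairs included after 22 weeks have no scheduled cerebral stills until 28 weeks or later

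*Protocol article*

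**What the plan says.** In the protocol article, Eligibility admits sFGR diagnosed before 28 weeks and explains the limit: "The upper inclusion limit of 28 weeks’ gestation was selected to capture both early and later presentations of sFGR".

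The text under Phase I: prenatal gives three study time points and includes the brain at each: "assessment of placental structure and fetal brain development are collected at inclusion (T1), 20–22 weeks (T2) and 28–30 weeks’ gestation (T3) (table 1". It then adapts the schedule for one case only: "If inclusion coincides with the second time point (20–22 weeks), only two assessments are performed".

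Table 1, which that text cites, differs. The row labelled "Inclusion (<28) (T1" has entries for flow, placenta and heart, but none for cerebral assessment or MRI. Cerebral imaging first appears in the T2 row: "Still images 3D volume (20–24 weeks". The row for 22–28 weeks contains only routine ultrasound under local protocol. The T3 row has stills at 28–32 weeks, a 3D volume at 28+0 weeks and MRI at 28–30 weeks; the text says MRI currently runs at selected centres only.

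Secondary outcomes include "Fetal brain development and neurodevelopment at 24 months". The Data analysis plan includes "Longitudinal modelling of ultrasound trajectories using mixed-effects models (continuous variables", stratified by gestational age at diagnosis, with cut-offs to be taken from the literature.

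**The concern.** A site cannot tell from the article whether an inclusion scan should contain cerebral images. For a pair included before 20 weeks this matters little, because T2 follows. For a pair included after the T2 window it decides whether any baseline brain image exists. The eligibility limit was set to bring such pairs in, and the adaptation rule does not cover them.

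Three things are at stake:

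- Within-fetus change in brain measures for late-included pairs needs two time points.
- The loss is selective. The late-included pairs left without any study fetal brain scan are those delivered, or both lost, before 28 weeks, and demise and early delivery for fetal distress make up the primary outcome.
- If some centres follow the text and others the table, missingness will differ by centre.

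A baseline scan that was not taken cannot be recovered later.

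**Working it through.** This is a check of the schedule; the plan states no figure to reproduce.

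**Text against table.** The text names fetal brain development without exception for T1, T2 and T3 and cites Table 1. The T1 row of Table 1 leaves the cerebral cell empty. The row has the same number of columns as its neighbours, so the gap does not look like a conversion fault. Both statements cannot describe the inclusion scan.

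**Table 1 read literally, by gestational age at inclusion.**

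| Inclusion | First scheduled stills | First scheduled 3D volume | If delivered or both lost before 28 weeks |
|---|---|---|---|
| Up to 22 weeks | T2 | T2 | T2 images, if T2 was reached |
| After 22, up to 24 weeks | T3 | Still within the 20–24 week window, but no study visit is scheduled to take it; otherwise T3 | No stills; a 3D volume only if a site takes one unprompted |
| After 24, before 28 weeks | T3 | T3 | No study-specific fetal brain scan |

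The wait from inclusion to the start of T3 is 28 minus the week of inclusion: 28 − 22.5 = 5.5 weeks, 28 − 24 = 4 weeks, 28 − 25 = 3 weeks. A pair included at 25 weeks thus has a study scan with Doppler, placental and cardiac measurements, and its first scheduled brain image at least three weeks later.

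**Share of pairs.** The article gives no distribution of gestational age at inclusion, so the share cannot be derived. Two assumed distributions show only how wide the uncertainty is:

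- Uniform over 16–28 weeks: after 22 weeks, (28 − 22)/12 = 50%; after 24 weeks, (28 − 24)/12 = 33%.
- Triangular over 14–28 weeks with peak at 18: the upper tail beyond g is (28 − g)²/[(28 − 14)(28 − 18)]. After 22 weeks this is 36/140 = 25.7%; after 24 weeks, 16/140 = 11.4%.

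**Who can still benefit.** Trial status reports 209 pairs enrolled by December 2025 and about 10 per month until the end of 2026. Twelve months at that rate is about 12 × 10 = 120 further pairs. Only the late inclusions among them, after the amendment takes effect, would gain a baseline scan.

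**Primary analysis.** Table 3 lists no cerebral measure among the candidate predictors, so the prediction model is untouched.

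**The case against.** The best defence is that this is a condensed article. The text introduces its list with a loose formula and defers to Table 1, the overview figure is not available here, and the full protocol may say what happens at late inclusion. That may explain the discrepancy, but the article still states two incompatible things, and its one adaptation rule omits the later inclusions that it says it wants.

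Several stronger readings are tempting, and the article does not support them:

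- *The inclusion visit has no cerebral assessment by design.* That is the table's version only; the text says the opposite.
- *Late-included pairs that reach the primary outcome have no brain data.* Phase II gives neonates cerebral ultrasound within 1–3 days, and Table 3 lists structures that overlap with the fetal measurements. After demise of one twin, the survivor can still be scanned at T3. The delivery component runs to below 32 weeks, so some events follow a T3 scan. For the same reasons, it does not follow that brain effects are seen only in milder survivors.
- *The brain objective cannot be answered in late-diagnosed pairs.* Comparing co-twins at T3, and relating antenatal to postnatal imaging, each need only one antenatal scan. Mixed models accept unequal numbers of observations. The stratum cut-offs are not fixed, and an early cut-off would put pairs scanned at T2 into the later stratum.

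What remains is that a pair with one time point carries no information on its own change, and that following the table loses baseline images selectively.

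**Conclusion.** The concern holds as a contradiction between text and Table 1, with a gap in the rule for late inclusion. If the table is followed, pairs included after 22 weeks lack scheduled stills, and those included after 24 weeks also lack a 3D volume, until 28 weeks or later. Those delivered, or both lost, before then have no study-specific fetal brain scan. The effect is confined to the fetal brain development outcome and any brain-measure trajectories in late-diagnosed pairs.

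The number affected is unknown. The assumed distributions put 26–50% of inclusions after 22 weeks and 11–33% after 24 weeks, and neither distribution comes from the article. If sites already follow the text, the gap in practice is smaller and the table is what needs correcting. The point merits an amendment because it is cheap and the lost images cannot be recovered. It does not threaten the primary aim.

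**What to change.** 1. Reconcile the Phase I text with Table 1. Fill the cerebral cell of the T1 row with stills and 3D volume for inclusion after the T2 window, except where inclusion is so close to T3 that the scan would duplicate it. If no cerebral images are intended when inclusion precedes T2, the text should say so.
2. Widen or annotate the 20–24 week 3D window so that a volume taken at late inclusion is within protocol.
3. Extend the sentence on inclusion at 20–22 weeks to inclusion after 22 weeks, stating which assessments are then done.
4. For late pairs already enrolled without a cerebral scan at T1, limit within-fetus brain trajectories to those with two cerebral time points, and describe T3 and MRI findings as conditional on still being in utero at 28 weeks.

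The cost is a short schedule amendment and a few extra minutes per late-inclusion scan; Table 2 puts the 3D acquisition at about 4 seconds per twin. The study scan already takes place, so no extra visit or staff is needed. The limitation is that items 1–3 help only pairs enrolled from now on; for the others, item 4 is all that can be done.
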